**Discussion:**

This study is the first to investigate whether individualized VR videos have additional benefits over generic VR nature videos on symptom relief, well-being, treatment satisfaction, and adherence in patients with palliative cancer care. A strength of the study is that we can incorporate the results of each part of the project into the subsequent project parts. However, the generalizability might be limited as this is a single-centred study.

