### Project part II: assessment of the experience with the individualized VR-intervention

Aim, study design and setting: In a prospective clinical cohort study, we assess the influence of personalized VR videos on symptoms, well-being, and vegetative functionality. Data will be collected using questionnaires and patient record analysis. First and foremost, we want to ensure patient safety. Thus, the aim is to prove a non-inferiority of the intervention in this vulnerable group and to start with 10 patients at least. Further, we want to observe whether ceiling effects occur in terms of well-being in this patient group, and to match the subjective verbal judgment of the patients regarding well-being after the VR-experience compared to baseline to reflect on the assumption that the minimally clinically important difference for well-being as assessed with the MDBF (Multi Dimensional Well-being Questionnaire) [21] is a 0.5 standard deviation or actually more prior to the sample size calculation for a power of 0.8 with a one sided significance level of 0.05, resp. effect size in a consecutive larger sample [22, 23]. This piloting is important because from our assumption so far the sample size would range between 30 and 130 participants [24, 25].

Participants: The same inclusion and exclusion criteria apply as in project part I.

Intervention: We create personalized VR videos as requested from the patients, probably from the patient’s home or family members. After the videos are created, the patients watch the videos using VR headsets while being cared for in a hospital unit. The videos are edited to a length of about 3–15 min. The patients watch the generic nature video for comparison before or after the personalized video (1:1 randomization). Before and after watching the videos, the patients answer the questionnaires using a tablet computer; support by a trained research assistant is provided to the comfort of the patients. The whole procedure of VR application takes about 20–30 min. If desired, patients can watch the personalized video repeatedly on different days for a maximum duration of 14 days. If patients are interested, they will be provided with the video file.

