Questionnaires: Symptom perception (minimal documentation system, MIDOS) [26], well-being (MDBF Multidimensional Well-Being Questionnaire) [21], subjective benefit of VR videos (2 self-developed items), cybersickness (SSQ Simulator Sickness Questionnaire) [27], presence experience (SPES Spatial Presence Experience Scale) [28].

In addition to interviewing patients after viewing VR videos, information on disease, treatment adherence, pain medication, and vegetative functionality will be collected from patient records to avoid further, potentially burdensome physical examinations during study participation.

Data analysis: The analysis is performed with the total data set reflecting the intention-to-treat principle. Descriptive methods are used for the analysis of all collected data (frequency distributions, mean, median, interquartile). For the pre/post comparisons of the outcomes (well-being, symptom perception, treatment experience, treatment adherence, pain medication, autonomic functionality), with well-being as the primary outcome, non-parametric Wilcoxon signed-rank t-tests for repeated measures data are calculated. Analysis is performed using IBM SPSS Statistics and R (r-project.org).

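### The only test stated for the primary outcome is pre/post, so the stated analysis does not address the added benefit over generic video that the abstract claims

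*Protocol article*

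**What the plan says.** **Question.** The Discussion paragraph of the Abstract presents the study in these terms: "This study is the first to investigate whether individualized VR videos have additional benefits over generic VR nature videos on symptom relief", and extends this to well-being, treatment satisfaction and adherence.

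**Design.** In Methods, Project part II, the Intervention paragraph states: "The patients watch the generic nature video for comparison before or after the personalized video (1:1 randomization". Each patient is therefore their own control and the order is randomised. This is a two-period crossover, although the same section calls part II a cohort study. On measurement it says: "Before and after watching the videos, the patients answer the questionnaires using a tablet computer". It does not say whether a questionnaire is completed between the two videos.

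**Analysis.** The Data analysis paragraph of part II begins its inferential statement with "For the pre/post comparisons of the outcomes" and continues: "with well-being as the primary outcome, non-parametric Wilcoxon signed-rank t-tests for repeated measures data are calculated". It also states: "Descriptive methods are used for the analysis of all collected data". No section names a contrast between the two videos, or a term for order or period.

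**Other aims.** The Aim paragraph of part II puts safety first: "the aim is to prove a non-inferiority of the intervention in this vulnerable group". It plans at least 10 patients to start with, to inform the sample size of a later, larger sample. The Background asks whether tailored videos are accepted and suitable.

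**The concern.** A change from before to after a personalised video can come from several sources: the individual content, any VR experience, the attention of the research assistant, expectation, or regression to the mean. A pre/post test responds to the sum of these. Only the comparison of the two videos within the same patient isolates individualisation, and that is the comparison which the randomised order protects.

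As written, the one p-value planned for well-being rests on a contrast that randomisation does not protect, and the randomised element serves no stated inferential purpose. A significant pre/post result, read beside the Abstract, would invite the conclusion that personalised videos add something over generic ones. The test gives no support for that.

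**Working it through.** **1. The plan's own figure.** The Aim paragraph of part II gives a provisional range of 30 to 130 participants, with a 0.5 SD difference, one-sided 0.05 and power 0.80. For a paired test, n = ((z₀.₉₅ + z₀.₈₀)/d)² = ((1.645 + 0.842)/0.5)² = 24.7, so 25; the t version gives 27 and the Wilcoxon version (efficiency 0.955) 28. This is close to the lower end. The upper end does not follow from the same inputs: two independent groups, one-sided, give 100 to 106 in total. The article does not say how 130 arose. Nothing ties either end to a personalised-minus-generic contrast.

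**2. What each contrast estimates.** Let P and G be a patient's MDBF change with the personalised and the generic video.
- Pre/post test: the hypothesis is P centred at 0. Write P = (effect common to both videos and to the setting) + (added benefit). The test can reject when the added benefit is 0.
- Between-video contrast: D = P − G. The common effect cancels and the added benefit remains.

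**3. Illustration.** Assumptions: P and G are independent, each normal with mean 0.5 and SD 1, so the added benefit is 0; one-sided 0.05; 4,000 simulated trials per sample size. The article gives the one-sided level for the later sample size calculation, and its analysis paragraph states no sidedness.

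| n | pre/post signed-rank significant | signed-rank on D significant |
|---|---|---|
| 10 | 38% | 3.8% |
| 30 | 84% | 5.0% |
| 130 | 100% | 5.5% |

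The middle column is the power of the pre/post test for a change that was assumed to be real. The last column is the nominal level. The table shows only that the first result carries no information about the second.

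**4. Order and period.** If period 1 differs from period 2 by δ, D has mean (added benefit + δ) in patients who see the personalised video first and (added benefit − δ) in the others. Averaging the two order-group means removes δ. Pooling without regard to order does so only when the groups are equal. At a 7:3 split the pooled mean carries (0.7 − 0.3)δ = 0.4δ. With 10 patients and simple randomisation, a split of 7:3 or worse has probability 2 × (1 + 10 + 45 + 120)/1024 = 0.34. The article does not state simple randomisation, so this figure is conditional on it.

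**5. Is the contrast measurable?** If the MDBF is completed before, between and after the two videos, P and G are both observed. If it is completed only before the first and after the last, just the combined change is observed and D cannot be formed. The article's wording allows either.

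**6. Precision of the contrast.** For an added benefit of 0.5 SD of the change score and correlation ρ between P and G (not given, assumed), d = 0.5/√(2(1 − ρ)). At one-sided 0.05 and power 0.80, n = 6.18/d²:
- ρ = 0: 6.18/0.125, so 50
- ρ = 0.5: 6.18/0.25, so 25
- ρ = 0.8: 6.18/0.625, so 10

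For a standardised difference of 0.25, n = 6.18/0.0625, so 99. With 10 patients, the 95% interval for the mean of D has half-width 2.262/√10 = 0.72 SD of D.

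**The case against.** The strongest reply is that added benefit is not the aim of part II. The wording appears once, in the Abstract. The Background speaks of acceptance and suitability, the part II aim is the influence of personalised videos with safety and non-inferiority, and the aim restated in the main Discussion names no generic comparator. For a pilot that starts with at least 10 patients, a change from baseline is a natural summary. This stands in part: a reader might infer that the whole article treats added benefit as its leading question, and it does not. But the Abstract does make the claim, and the generic video is included expressly for comparison. Claim and stated test must be brought into line one way or the other.

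Secondly, a reader might infer that the between-video comparison is excluded. The documents do not say so. Descriptive methods cover all data, and the main Discussion reports that the biometrics institute recommended them, so a descriptive comparison may well be intended. What remains is that the one formal analysis named for the primary outcome is a different contrast. This is more than detail left to a fuller plan, because the article itself fixes the outcome, the test and the contrast.

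Thirdly, the percentages in the table are largely built in by the assumed 0.5 SD change. That is correct, and they should not be read as false-positive rates.

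Fourthly, the remedy may not be free. It needs a measurement between the videos that the article does not clearly provide, and at small n the contrast is imprecise. Both points stand. Carry-over from the first video to the second would also remain a limitation, since the procedure takes about 20–30 minutes and no washout is stated.

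**Conclusion.** The point holds in a limited form. The article claims to investigate added benefit over generic video and randomises the order of two videos within each patient, but the only test it states for well-being is pre/post, which does not bear on added benefit. If both videos helped equally, that test could still be significant: 38% of trials at n = 10 and 84% at n = 30 under the assumed 0.5 SD change with both videos.

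A reader might infer that the trial cannot answer the question. The documents do not support that. The design can answer it, provided the MDBF is recorded around each video; it is the stated analysis that does not. Nor do they show that order imbalance will bias the result, because the method of randomisation is not described and no order-blind between-video contrast is planned.

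The mismatch concerns the primary outcome and the main claim, so it should be resolved before the data are analysed.

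**What to change.** 1. For the added-benefit question, specify the within-patient difference in MDBF change, personalised minus generic, as the analysis, with the randomised order and period taken into account. One way is to average the mean differences of the two order groups; a rank-based or mixed-model equivalent would also serve. Report an estimate with a confidence interval.
2. Keep pre/post change, separately for each video, for the safety and pilot aims.
3. State that the MDBF is completed before and after each video, and describe part II as randomised in order.
4. If the MDBF is not completed around each video, or if part II stays a small safety pilot, limit the Abstract's claim to pre/post change and drop the added-benefit wording.

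**Cost.** If the MDBF is already completed around each video, only wording changes. If not, one further short questionnaire falls between the videos, a burden to weigh in this population. At about 10 patients the contrast should be reported as an estimate and not as a test. A confirmatory comparison would need a sample size set for this contrast: 25 to 50 patients for a 0.5 SD added benefit at assumed correlations of 0.5 to 0, and about 99 for a standardised difference of 0.25.

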### Project part III: PPI to inform VR implementation in palliative cancer care

Aim, study design and setting: PPI will be used for a reciprocal exchange of findings, and the further implementation of the individualized approach for VR in palliative cancer care.

Participants and procedure: Patients, patients’ family members, the patient advisory board, and healthcare professionals from the participating hospital departments are invited to exchange views on strengths, weaknesses, opportunities and threats (SWOT) in the context of implementation of the personalized VR intervention based on the results from the project part II.

Data analysis: We structure the results from the discussion by a SWOT analysis (strength, weaknesses, opportunities, threats) to inform an implementation strategy.

### Data management and dissemination

#### Confidentiality

The names of participants and all other confidential information are subject to medical confidentiality and the provisions of the Data Protection Regulation (Datenschutzgrundverordnung DSGVO) and the State or Federal Data Protection Act (LDSG or BDSG). Data collected during the study will be kept anonymously in accordance with good scientific practice for 10 years after the end of the study (until 2034). The data will be used exclusively for the purposes of this study. All data will be stored pseudonymously in access-restricted drives on secured computers and servers of the University of Heidelberg and the University Hospital, Department of Palliative Care, of the scientists involved in the project. The pseudonymization keys as well as signed consent forms are stored in the locked steel cabinet of a project partner (CW). A digital file of the pseudonymization key, which contains only ID and name of the participating persons, is double password protected and stored in the secure sync-and share service for collaboration within the university, hosted locally in the cloud by the university data center. Only the scientists involved in the project have access to the pseudonymization keys.

Participant data may only be passed on in pseudonymized form, which is anonymized by destroying the pseudonymization list three months after the end of the data collection. Third parties are not given access to original documents.

#### Dissemination policy

Study results will be published in peer-reviewed, indexed, journals using an open access format, and the results will be presented at national and international conferences. Authorship eligibility will be in accordance with The International Committee of Medical Journal Editors. The National Center for Tumor Diseases Heidelberg foundation supports this study and we will work with them and the Patient Advisory Board to disseminate findings easily accessible for patients and healthcare professionals.

## Discussion

This study aims to investigate whether individual VR videos provide benefits in terms of symptom relief, well-being, treatment satisfaction, and treatment adherence in palliative cancer care. The novelty of this project are the individualized VR videos as in previous research with palliative patients only generic videos, such as nature shots, were used.

A further strength of the study is that the patients’ opinions as well as those of the relatives and the patient advisory board are considered, i.e., heavily involving those concerned by the intervention in its development. The combination of qualitative and quantitative method allows to inform the subsequent project parts: In the first part, we start with qualitative interviews to gain an in-depth understanding of the topic. We ask not only about wishes and needs, but also about worries and concerns. The results of the first part enable us to respond with a high degree of flexibility to the needs of the patients in the second part of the study. Moreover, we ensure patient safety when we assess and compare cybersickness, symptoms, and use of medication for symptoms before and after the intervention with no tolerance for a decline of the patient’s subjective wellbeing. The study is designed to implement VR video use tailored to the needs of patients feasible not only under laboratory conditions but in everyday clinical practice.

However, the generalisability of our study results will be limited because we perform a single centre study. Nevertheless, the experiences from the project may inform others who want to adapt the intervention to their site or to other palliative care samples. In terms of the sample, we suspect that particularly highly burdened patients will not participate in the study, although they would like to use the VR intervention outside of a trial. For this reason, we involve relatives and the patient representatives’ experiences and attitudes as a proxy. Whether older patients will be more likely to decline study participation because of restraints towards new technology is an apprehension that could not be clarified in former studies applying VR interventions to older people [29], and we aim to consider the particular needs of vulnerable and old people to operate the VR intervention.

The NCT funding board reviewed a summary of this study to ensure its aims and objectives, study design and outcome are suited and promising to improve the care of cancer patients. The Institute for Biometrics of the Heidelberg University Hospital reviewed the quantitative data analysis plan and recommended descriptive methods. The anthropologist and research coordinator of the Department of Palliative Care of the Heidelberg University Hospital reviewed the protocol regarding the qualitative methodology and mixed methods approach. Further, three members of the NCT patient advisory board informed the interview guide, the selection of questionnaires, and the sheets for informed consent. They found it important to explore the potential of individualized VR-videos to alleviate the situation of palliative inpatients with cancer. In this context, they welcomed the approach to find out the wishes and concerns of patients and relatives related to the intervention to guide its implementation.

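### The planned pre/post tests cannot support a claim that VR itself is beneficial, because both viewing conditions are VR; any benefit conclusion should rest on personalised versus generic video

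*Protocol article*

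**What the plan says.** The question is put in two ways.

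- **Benefit or influence as such.** The Discussion says: "This study aims to investigate whether individual VR videos provide benefits in terms of symptom relief, well-being, treatment satisfaction, and treatment adherence". The aim paragraph of Project part II reads: "In a prospective clinical cohort study, we assess the influence of personalized VR videos on symptoms, well-being, and vegetative functionality". Neither sentence names a comparator.
- **Benefit beyond generic VR.** The Abstract's Discussion says: "This study is the first to investigate whether individualized VR videos have additional benefits over generic VR nature videos".

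The Intervention paragraph of Project part II gives the design: "The patients watch the generic nature video for comparison before or after the personalized video (1:1 randomization". All patients therefore see both videos. Assessment is described as "Before and after watching the videos, the patients answer the questionnaires using a tablet computer", and "support by a trained research assistant is provided to the comfort of the patients". The whole procedure takes about 20–30 minutes, and the personalised video may be watched again on other days for up to 14 days.

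The Data analysis paragraph of Project part II begins its inferential part with "For the pre/post comparisons of the outcomes" and names Wilcoxon signed-rank tests, with well-being as primary outcome. It names no comparison between the two videos.

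**The concern.** The aim, the design and the named test do not line up. The design can answer whether a personalised film adds something to a generic VR film. The Discussion asks whether personalised VR helps at all, and the named test looks only at change from before to after.

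That change has several parts besides any effect of VR: the attention of the research assistant, expectation about a film made at the patient's own request, and answering the same questionnaires twice. No condition in the design shows what these produce without VR. A larger follow-on sample does not help: the non-specific part does not shrink, while the test becomes more likely to detect it.

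At stake is what Part II can conclude about its primary outcome. The limitations named in the Discussion are the single centre and the likely non-participation of highly burdened patients; the lack of a VR-free comparison is not among them.

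**Working it through.** **1. What each comparison can show**

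| Comparison | Contains | Question answered |
|---|---|---|
| After minus before (the named test) | VR effect + attention + expectation + repeated questioning | None cleanly; descriptive only |
| Change with personalised minus change with generic video | Effect of personal content; shared session influences cancel | The Abstract's question |
| VR versus no VR | Not in the design | The Discussion's question as worded |

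**2. The plan's own sample size figure**

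The Part II aim paragraph gives a provisional range of 30 to 130 for a later, larger sample, with 0.5 SD, power 0.8 and one-sided 0.05. For a paired comparison, n = ((1.645 + 0.842)/0.5)² = 24.7, so 25. The t version gives 27. Dividing by the Wilcoxon efficiency gives 27/0.955 = 28.3, so 29, or 27/0.864 = 31.3, so 32. This agrees with the lower end. The inputs for the upper end are not stated. The range is not disputed here; it only supplies sample sizes for the illustration.

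**3. Illustration: how often a pre/post test declares benefit when VR does nothing**

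Inputs from the protocol article, Part II aim paragraph: a start with at least 10 patients; 30 and 130 as above; one-sided 0.05. That level is stated for the later sample size calculation, and its use for the planned tests is an assumption. Further assumptions: no VR effect, normally distributed changes, and a non-specific gain d of 0.2 or 0.3 SD of change. The documents give no value for d.

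The t version uses the probability that a noncentral t with n − 1 degrees of freedom and noncentrality d√n exceeds the one-sided 5% critical value. For n = 30 the noncentrality is 0.2 × 5.477 = 1.095 or 0.3 × 5.477 = 1.643. The signed-rank version is a simulation with 3,000 runs.

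| n | d | d√n | t-test | Signed-rank, pre/post | Signed-rank, personalised minus generic |
|---|---|---|---|---|---|
| 10 | 0.2 | 0.632 | 14.5% | 12.3% | 3.3% |
| 10 | 0.3 | 0.949 | 22.2% | 19.6% | 4.0% |
| 30 | 0.2 | 1.095 | 28.3% | 28.2% | 4.6% |
| 30 | 0.3 | 1.643 | 48.4% | 46.2% | 4.3% |
| 130 | 0.2 | 2.280 | 73.4% | 72.1% | 5.5% |
| 130 | 0.3 | 3.421 | 96.1% | 95.5% | 5.1% |

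With no drift, the simulated pre/post signed-rank test rejects in 3.2%, 5.2% and 6.0% of runs at n = 10, 30 and 130. The last column gives both videos the same non-specific gain. Under that assumption the contrast stays near its nominal level or below it.

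**The case against.** **The design has a control.** The generic video shares the headset, the session and the assistant, and its order is randomised. For the Abstract's question no VR-free arm is needed. The Discussion also places the novelty in individualisation, since earlier work used generic films. This stands. A reader might infer that the trial is uncontrolled or must add a non-VR arm. The documents do not support that; the control is there, but the named analysis does not use it.

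**Part II starts as a safety pilot.** It begins with at least 10 patients, puts safety and non-inferiority first, and precedes any final sample size. The Discussion also reports that the biometrics institute recommended descriptive methods. This limits the weight of the point for the pilot. It does not remove it, because the Data analysis paragraph still plans tests and the stated aim is still benefit.

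**Some mechanisms are weak.** A reader might put regression to the mean and passage of time on a par with attention. Entry is not selected on low well-being, and patients in poor condition or too stressed are excluded, so regression to the mean is minor and could even run against a benefit. The session lasts 20–30 minutes, which leaves little room for spontaneous change in well-being. Time matters more for adherence and medication, which are taken from records.

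**The rates depend on an assumed gain.** This is correct. They show direction and growth with n, not a forecast.

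**Conclusion.** The point holds as a mismatch between aim, design and named test. Pre/post change cannot separate a VR effect from attention, expectation and repeated questioning, so it cannot carry a claim that VR is beneficial in itself. If the non-specific gain were 0.2 to 0.3 SD of change and VR had no effect, the signed-rank test would declare benefit in about 12–20% of trials at n = 10, 28–46% at n = 30 (t-test up to 48%) and 72–96% at n = 130, against a nominal 5%. Only n = 10 describes the pilot; the others belong to a provisional range for a later sample.

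A reader might infer that a significant pre/post result will be published as proof that VR works. The article does not say so. What it does is leave that reading open, by wording the aim without a comparator and naming no other test.

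**What to change.** 1. In the Part II aim and Data analysis paragraphs and in the Discussion, state that pre/post change is an uncontrolled description and that no absolute benefit of VR will be claimed from it.
2. Align the aim with the Abstract: benefit of personalised over generic VR.
3. Name the within-patient contrast of the two videos as the basis for any benefit conclusion on well-being and symptoms. This requires questionnaires around each video; the article does not make clear whether they are taken between the two, and this should be stated.
4. Keep adherence and medication from the records descriptive. Both videos appear to fall within one procedure, and repeat viewing is of the personalised film only, so changes over days cannot be assigned to one video.

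An additional questionnaire at consent is not recommended. The change from consent to session would span the making of the film, an interval of unstated length that includes anticipation of it. It would not control for attention in the session, and it would add burden for palliative inpatients.

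The cost is wording and, if not already planned, one assessment between the videos. The downside is that the conclusion is limited to benefit over generic VR. The contrast also does not remove any expectation that attaches specifically to the patient's own film.

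### The no-tolerance statement on declining well-being has no patient-level analysis behind it: the planned signed-rank test can show improvement while individual patients clearly worsen

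*Protocol article*

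**What the plan says.** **Methods, Project part II, aim.** Safety heads the aims: "First and foremost, we want to ensure patient safety". It is then put as a non-inferiority aim: "the aim is to prove a non-inferiority of the intervention in this vulnerable group". The study starts with at least 10 patients. The same paragraph assumes an important difference of 0.5 SD on the MDBF, and plans "to match the subjective verbal judgment of the patients regarding well-being after the VR-experience compared to baseline" as a check on that assumption.

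**Methods, Project part II, data analysis.** The pre/post comparisons cover six outcomes ("well-being, symptom perception, treatment experience, treatment adherence, pain medication, autonomic functionality"), "with well-being as the primary outcome". For these, "non-parametric Wilcoxon signed-rank t-tests for repeated measures data are calculated". In addition: "Descriptive methods are used for the analysis of all collected data (frequency distributions, mean, median, interquartile"). The SSQ is collected, but cybersickness is not among the six outcomes named for pre/post testing.

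**Discussion.** Patient safety is said to be ensured by comparing cybersickness, symptoms and symptom medication "before and after the intervention with no tolerance for a decline of the" patient's subjective well-being.

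The article does not define a decline in an individual patient. It does not say that patients who decline will be counted, or how such a count would bear on the safety conclusion.

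**The concern.** The Discussion speaks of the patient in the singular and allows no decline. The Methods speak of non-inferiority, which is a group-level idea. The analysis is a test of group location. These three statements are not reconciled, and the analysis does not match the first of them if it is read per patient.

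A signed-rank test adds the ranks of gains and sets them against the ranks of declines, so a few marked deteriorations can be outweighed by many moderate gains. Separate before and after summaries (mean, median, quartiles, frequencies) do not show who worsened either, because the pairing is lost.

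Viewing one's own home might comfort most inpatients and distress a few; the article itself allows for emotional distress even in the part I interviews. A harmed minority is the result that a location measure hides. The study could then report improved well-being beside its no-tolerance statement while its own data showed clear worsening in some patients.

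**Working it through.** The plan gives no figure for this point, so there is none to reproduce. Inputs from the Methods for part II: 10 patients at the start; 30 as the lower end (130 as the upper end) of the provisional later sample; one-sided 0.05; an assumed important difference of 0.5 SD.

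**1. Exact signed-rank p with 10 patients.** With no ties, one-sided p = (number of subsets of the ranks 1 to 10 whose sum is at most the negative rank sum) / 2^10. The subsets with sum 0, 1, ..., 10 number 1, 1, 1, 2, 2, 3, 4, 5, 6, 8, 10, in total 43. A negative rank sum of 10 therefore gives p = 43/1024 = 0.042, and a sum of 11 gives 0.053. Two arrangements reach 10:
- One patient has the largest change of all, a deterioration (rank 10), and the other nine improve.
- Four patients decline by the four smallest amounts (1 + 2 + 3 + 4 = 10).

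At two-sided 0.05 the limit is a negative rank sum of 8 (p = 0.049). The patient with the third-largest change could still be a decliner, or three patients could decline slightly (1 + 2 + 3 = 6, p = 0.027).

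**2. With 30 patients.** If the five largest changes are all deteriorations, the negative rank sum is 26 + 27 + 28 + 29 + 30 = 140 and the exact one-sided p is 0.029. With the six largest (sum 165) it is 0.085.

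**3. How usual this is.** This step rests on my assumption of normal changes in units of the reference SD. P(decline) = Φ(−mean/SD of change), P(decline of at least 0.5) = Φ((−0.5 − mean)/SD of change), and P(at least one of 10) = 1 − (1 − P)^10. An SD of change of 1 corresponds to a before/after correlation of 0.5, and 0.71 to a correlation of 0.75.

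| Mean gain | SD of change | Decline | At least one of 10 | Decline ≥ 0.5 SD | At least one of 10 |
|---|---|---|---|---|---|
| 0.5 | 1 | 30.9% | 97.5% | 15.9% | 82.2% |
| 1.0 | 1 | 15.9% | 82.2% | 6.7% | 49.9% |
| 0.5 | 0.71 | 24.0% | 93.5% | 7.9% | 55.9% |
| 1.0 | 0.71 | 7.9% | 55.9% | 1.7% | 15.7% |

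In a simulation of the first row (4,000 runs of 10 patients), 94% of the results significant at one-sided 0.05 contained at least one decliner, and 57% contained a decline of at least 0.5 SD.

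**4. What a count could show.** With 0 decliners of n, the one-sided 95% upper limit is 1 − 0.05^(1/n): 25.9% for 10 patients, 9.5% for 30, 2.3% for 130. The two-sided 95% Clopper-Pearson upper limit for 0 of 10 is 1 − 0.025^(1/10) = 30.8%.

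**The case against.** Several stronger readings are tempting, and the article does not support them.

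- **That safety is defined per patient.** It is not. The sentence stands in the Discussion, without threshold, instrument or decision rule, and the operative aim in the Methods is non-inferiority. The sentence could mean a zero margin at group level, which a one-sided location test would address. A literal zero-decline rule would fail in most pilots even under real benefit (step 3), so it is unlikely to be what was meant.
- **That the signed-rank shift is the only endpoint.** It is a test, not an endpoint. Six outcomes are compared, further instruments are collected, and all data are described, including by frequency distributions. Verbal judgments are also matched to baseline. But the frequency distributions are not said to be of individual change, and the stated use of the verbal judgments is to check the 0.5 SD assumption.
- **That the step to the larger sample hangs on this p-value.** Nothing says so. The pilot's further stated purposes are to look for ceiling effects and to review the important difference before the sample size calculation.

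It is also fair to say that the one-sided 0.05 belongs to the later sample size calculation and not to the first 10 patients, that the arrangements in steps 1 and 2 are constructed and show a property of any location test, and that the full protocol or SAP may hold a per-patient listing.

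What remains is that the article makes a safety statement in patient-level words and describes an analysis that cannot bear it in that sense.

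**Conclusion.** The point holds in a limited form. Read per patient, the no-tolerance statement cannot be supported by the planned group-level test, or by before and after summaries that are not of individual change. With 10 patients, a one-sided p of 0.042 for improvement is compatible with one patient having the largest change of all as a deterioration, or with four slight declines. These figures are exact for untied data. How often decliners accompany a significant result depends on the assumed normal model, and the table shows the range. If the statement is meant at group level, the defect is one of wording: it is not reconciled with the non-inferiority aim and gives no criterion. Either way the study's first-named aim would be better served by a count of patients who worsen. This is a worthwhile and cheap change; it does not invalidate the design.

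**What to change.** 1. Add a prespecified descriptive safety analysis to the part II data analysis: the number and proportion of patients whose MDBF worsens by at least 0.5 SD from before to after viewing, with an exact Clopper-Pearson interval. State which SD is the reference. Because each patient sees two videos, state which before/after pair is used.
2. Show individual pre/post changes on MDBF, MIDOS and SSQ alongside. Counts of any worsening should be descriptive only, because ordinary score fluctuation makes at least one decline among 10 patients likely even under benefit (56% to 97.5% in the table).
3. Reword the Discussion sentence so that it agrees with the non-inferiority aim in the Methods and claims no more than the interval can show. With 0 of 10, the one-sided 95% upper limit is still 26%.

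The cost is a few lines of text and one table, with no new data or burden on patients. The downside is a less favourable safety statement, since the interval is visibly wide at 10 patients.
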